## Abstract

**Background:**

Mild cognitive impairment (MCI) is a syndrome preceding more severe impairment characterized by dementia. MCI affects an estimated 15% to 20% of people older than 65 years. Nonpharmacological interventions including exercise are recommended as part of overall MCI management based on the positive effects of exercise on cognitive performance. Interval training involves brief intermittent bouts of exercise interspersed with short recovery periods. This type of exercise promotes cognitive improvement and can be performed in individuals with MCI. Synaptic plasticity can be assessed in vivo by the neurophysiological response to repetitive transcranial magnetic stimulation (rTMS). A method to assess synaptic plasticity uses an intermittent theta burst stimulation (iTBS), which is a patterned form of rTMS. Individuals with MCI have decreased responses to iTBS, reflecting reduced synaptic plasticity. It is unknown whether interval training causes changes in synaptic plasticity in individuals living with MCI.

**Objective:**

This research will determine whether interval training performed using a cycle ergometer enhances synaptic plasticity in individuals with MCI. The three aims are to (1) quantify synaptic plasticity after interval training performed at a self-determined intensity in individuals with MCI; (2) determine whether changes in synaptic plasticity correlate with changes in serum brain-derived neurotrophic factor, osteocalcin, and cognition; and (3) assess participant compliance to the exercise schedule.

**Methods:**

24 individuals diagnosed with MCI will be recruited for assignment to 1 of the 2 equally sized groups: exercise and no exercise. The exercise group will perform exercise 3 times per week for 4 weeks. Synaptic plasticity will be measured before and following the 4-week intervention. At these time points, synaptic plasticity will be measured as the response to single-pulse TMS, reflected as the percent change in the average amplitude of 20 motor-evoked potentials before and after an iTBS rTMS protocol, which is used to induce synaptic plasticity. In addition, individuals will complete a battery of cognitive assessments and provide a blood sample from the antecubital vein to determine serum brain-derived neurotrophic factor and osteocalcin.

**Results:**

The study began in September 2023.

**Conclusions:**

The proposed research is the first to assess whether synaptic plasticity is enhanced after exercise training in individuals with MCI. If exercise does indeed modify synaptic plasticity, this will create a new avenue by which we can study and manipulate neural plasticity in these individuals.

**Trial Registration:**

ClinicalTrials.gov NCT05663918; https://clinicaltrials.gov/study/NCT05663918

**International Registered Report Identifier (IRRID):**

PRR1-10.2196/50030

## Introduction

Memory impairment has long been seen as a common consequence of aging, but it could be seen as mild cognitive impairment (MCI), a precursor of dementias such as Alzheimer disease. MCI is characterized by evidence of cognitive decline without a substantial disruption to completing everyday tasks [1,2]. Currently, 15% to 20% of people aged 65 or older are living with MCI [3]. About 10%-15% of individuals with MCI progress to dementia [3], exacerbating the concern for reduced social and functional capacities of such a large number of people and their increased rate of mortality [1,2].

Risk factors for MCI include older age, sedentary lifestyle, low number of years of education, and factors such as hypertension and obesity, various cardiovascular diseases, and neuropsychiatric conditions including depression and anxiety [1]. MCI is recognized as an intermediate phase between a healthy brain state and dementia; however, not all individuals diagnosed with MCI are certain to progress to dementia, and some may even revert to normal life [4]. The progression to dementia is often preceded by subtle difficulties in performing everyday activities [5] and can include diagnoses of subjective cognitive impairment [6], mild behavioral impairment [7,8], and psychiatric disturbances including anxiety [9,10], depression [11-13], and posttraumatic stress disorder [14,15]. Amidst ongoing challenges in developing disease-modifying drugs, nonpharmacological interventions including exercise are recommended as part of the overall MCI management [16] based on the positive effects of exercise on cognitive performance [17-23].

Exercise promotes cognitive improvement [24-32], and individuals living with MCI can participate in various forms of exercise [33,34]. Evidence also supports the notion that exercise interventions have a positive influence on different facets of cognitive function in MCI such as global cognitive functioning [30], immediate recall [22,26-28], delayed recall [26], and executive function [31,32]. However, not all studies report improvements in cognitive performance following exercise training [35-37]. Further, physical exercise may present challenges related to mobility and movement that limit the accessibility of the intervention to all individuals. Nonetheless, physical exercise is an affordable and alternative approach to alleviate symptoms of cognitive decline [17-22,38,39].

Interval training can involve intermittent bouts of exercise performed at either a prescribed or self-determined intensity, interspersed with short recovery periods [40,41]. The latter enables participants to determine their own pace that they deem appropriate and tolerable. They are typically encouraged to identify a pace that is physically challenging and to rate their effort level or perceived exertion. This type of training can be performed by participants with a wide age range who are both healthy and have conditions such as type 2 diabetes [42-44], coronary artery disease [45,46], and obesity [47]. Evidence that aerobic-based interval training can improve cognitive function [24-32] suggests that cognitive improvement could be induced by aerobic interval exercise via upregulation of pathways that promote synaptic plasticity.

Synaptic plasticity involves activity-induced changes in specific patterns of neural activity that alter the strength or efficacy of synaptic transmission, playing a considerable role in the acquisition of information and learning of new behaviors [48]. Synaptic plasticity is modeled by long-term potentiation (LTP) and long-term depression (LTD). LTP increases synaptic transmission as a consequence of high-frequency stimulation of excitatory synapses or the correlation of presynaptic activity and postsynaptic depolarization [48]. In contrast, LTD decreases the strength and efficacy of synaptic transmission [49]. A significant association has been found between LTP, LTD, and age-related cognitive decline. Animal models have shown that reductions in cognition due to age correlate with reductions in the LTP originating in the hippocampus [49].

In humans, synaptic plasticity, and more specifically, LTP-like effects can be assessed in vivo by delivery of transcranial magnetic stimulation (TMS) in protocols called intermittent theta burst stimulation (iTBS) and 5-Hz repetitive TMS (5-Hz rTMS). Both forms delivered over the motor cortex induce LTP-like effects as measured by short-term increases in the efficacy of the corticospinal pathway from cortex to muscle [50,51]. These effects are analogous to animal models of LTP since they are mediated by glutamate and require glutamate binding at *N*-methyl-D-aspartate (NMDA) receptors [51]. In humans, the decline in neuronal excitability and synaptic function seen with aging contributes to memory loss as well as sensory and motor deficits [52]. Thus, in humans, iTBS and 5-Hz rTMS are noninvasive tools to assess whether aging and MCI populations demonstrate synaptic plasticity and whether interventions such as exercise can enhance the magnitude of synaptic plasticity. Compared to age-matched controls, individuals with MCI demonstrate blunted synaptic plasticity as indicated by a reduced response to 5-Hz rTMS [53] and iTBS [54]. These effects are reflected as decreases in motor evoked potentials (MEP) when compared to healthy controls. Healthy controls demonstrate MEP facilitation, as expected, observed by an increase in MEP amplitude during the delivery of a 5-Hz train. In contrast, 5 Hz–induced MEP facilitation is not seen in individuals with MCI, suggesting deficits of glutamate pathways responsible for synaptic potentiation [53]. The delivery of iTBS has yielded similar results in patients with MCI, demonstrating a lack of MEP facilitation [54].

Brain-derived neurotrophic factor (BDNF) is a key regulator of processes crucial for cognition, particularly learning and memory [55-57]. The presynaptic release of BDNF influences the activation, trafficking, and expression of NMDA receptors as a result of enhanced calcium influx. This calcium influx is thought to allow for the release of BDNF at the postsynaptic terminal. Postsynaptic BDNF release is essential for presynaptic vesicle cycling, which increases synaptic plasticity, ultimately leading to improvements in cognitive functioning [58]. BDNF expression is correlated with cognitive function [57] and is consistently elevated following exercise in healthy older adults, suggesting that the rise in BDNF levels with long-term exercise may reduce mental deterioration in patients with MCI [55].

Exercise increases the secretion of hormones and other factors into the blood from organs such as skeletal muscle, bone, and liver [59-70]. Some of these are known to increase brain BDNF either directly or indirectly. A bone-derived hormone called osteocalcin (OCN), which plays a role in bone mineralization and glucose metabolism, increases following exercise [71-75] and increases BDNF transcription and the number of BDNF vesicles transported to the synapse [76,77]. OCN is carboxylated at 3 different residues and is found in the blood in both carboxylated and partially or fully decarboxylated forms. Acute exercise increases the partially or fully decarboxylated forms of OCN in serum [72-75].

The proposed research will determine whether interval training performed at a self-determined intensity will enhance synaptic plasticity in individuals with MCI. The three aims are to (1) quantify synaptic plasticity after interval training performed at a self-determined intensity in individuals with MCI; (2) determine whether changes in synaptic plasticity correlate with changes in serum BDNF, OCN, and with cognition; and (3) assess compliance to the exercise schedule.

## Methods

### Screening

To determine the eligibility of those who have reached out to the study team via advertisements, individuals will be contacted to schedule a phone interview. During the phone interview, individuals will be provided with the details of the study, and eligibility for TMS will be assessed via a TMS screening questionnaire. Individuals will also be asked whether they have been diagnosed by a health care professional or physician with “Mild Cognitive Impairment” or “Mild Neurocognitive Disorder?” If the individual answers “Yes,” then they will be asked to provide a written medical note to confirm a diagnosis of MCI at the first scheduled session. In addition, the individual’s eligibility to complete the exercise protocol will be assessed using the Canadian Society for Exercise Physiology Get Active Questionnaire (GAQ). If the individual has contraindications to the GAQ, the participant will be asked to contact their family doctor and acquire a medical note clearing them for participation. The parameters of the study, including the procedures and collection measures, will be explained verbally to the participant. If the participant agrees to participate in the study and has no contraindications to the GAQ and TMS screening questionnaire, a time will be arranged for the individual to undergo the experiment. Participants will provide informed written consent on the day of data collection prior to any testing, as well as verbal reaffirmation before each procedure. Researchers will determine the capacity to consent for all participants at the commencement of the study, using a modified University of California, San Diego Brief Assessment of Capacity to Consent questionnaire.

### Ethical Considerations

Approval to conduct this study was granted by the Hamilton Integrated Research Ethics Board (ID # 14938) in partnership with Hamilton Health Sciences and conformed to the Declaration of Helsinki. In addition, this study has been registered and approved as a registered clinical trial on clincialtrials.gov (NCT05663918) in December 2022, a World Health Organization (WHO) accredited trial registry.

### Power

This pilot study will recruit 24 participants aged 55-80 years old diagnosed with MCI. To determine this sample size, the following features were included in an a priori calculation using G*Power (Heinrich-Heine-Universität Düsseldorf), α=.05, Power (1-β)=0.9, and the effect size was calculated using Trebbastoni et al’s findings [53].

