### Experimental Design

Individuals will be recruited for assignment to 1 of the 2 equally sized groups: exercise or no exercise. The exercise group will perform the exercise intervention. The no exercise group will serve as the control.

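### The 90% power claimed for 24 participants is unsupported for the planned test: its effect size comes from a study described only as MCI versus age-matched controls under 5-Hz rTMS

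*Protocol article*

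**What the plan says.** The Power section gives the sample size: "This pilot study will recruit 24 participants aged 55-80 years old diagnosed with MCI". It presents this number as the result of an a priori G*Power calculation with "α=.05, Power (1-β)=0.9, and the effect size was calculated using" reference 53. It prints no effect size, standard deviation, test family or sidedness.

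The Introduction says what reference 53 found: "Compared to age-matched controls, individuals with MCI demonstrate blunted synaptic plasticity as indicated by a reduced response to 5-Hz rTMS [53] and iTBS [54". The same paragraph explains that facilitation in healthy controls was "observed by an increase in MEP amplitude during the delivery of a 5-Hz train", and that it was absent in MCI. The iTBS result is credited to a different source, reference 54.

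The trial's own design differs. Under Experimental Design, "Individuals will be recruited for assignment to 1 of the 2 equally sized groups: exercise or no exercise", and all participants have MCI. The Methods part of the Abstract defines the plasticity measure as the "percent change in the average amplitude of 20 motor-evoked potentials before and after an iTBS rTMS protocol". The Statistical Analysis Plan section then compares the T0 to T1 percentage change in plasticity between the two groups with an unpaired t test at the .05 level.

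**The concern.** A power statement is meaningful only if its effect size refers to the contrast and outcome that will be tested. Here the named source, as the article describes it, differs from the planned test in three respects:

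- **Contrast:** MCI against healthy controls, not exercise against no exercise within MCI.
- **Stimulation:** MEPs during a 5-Hz train, not MEPs before and after iTBS.
- **Outcome:** a difference between populations in their response, not a change between two visits four weeks apart.

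The first and third matter most. How far patients lie from healthy people does not say how far four weeks of cycling will move them. The Conclusions of the Abstract call this the first study of whether exercise training enhances synaptic plasticity in MCI, so by its own account there was no direct exercise effect to borrow.

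At stake is how the result is interpreted. The article sets a significance test and says in its closing Conclusions that the study will determine whether exercise alters plasticity. A stated power of 90% tells the reader how much weight a non-significant result can bear, and here that figure has no basis for the question asked.

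**Working it through.** **Inputs from the protocol article.** Total 24 in two equal groups, so n = 12 per arm (Power; Experimental Design). Alpha .05 and power 0.9 (Power). Unpaired t test on the T0 to T1 change (Statistical Analysis Plan). The effect size and the sidedness are not stated.

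**Reproducing the plan's figure.** This is not possible going forward, because no effect size is printed. It can only be solved backwards for the standardised difference d that 24 participants would need.

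**Formula.** The t statistic has 2n − 2 = 22 degrees of freedom and noncentrality d × √(n/2) = d × √6. Power is the probability that this noncentral t exceeds the critical value, which is 2.074 two-sided or 1.717 one-sided.

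| n per arm | Sides | d for 80% power | d for 90% power |
|---|---|---|---|
| 12 | two | 1.20 (1.197) | 1.39 (1.385) |
| 12 | one | – | 1.23 (1.233) |
| 10 | two | 1.32 (1.325) | 1.53 (1.534) |

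**Power with 12 per arm, two-sided, at other values of d:** 0.5 gives 22%; 0.8 gives 47%; 1.0 gives 65%; 1.2 gives 80%. One-sided at 0.8, power is 60%. The documents give no effect of exercise on this outcome, so these values are a range and not estimates.

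**Precision.** The 95% confidence interval for the difference in mean change has half-width t(0.975, 22) × √(2/12) = 2.074 × 0.408 = 0.85 SD of the change.

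**Illustration of carrying a single-visit gap over to a change score.** Three assumptions are not in the documents: the MCI-to-control gap is 1.385 SD (solved back from n = 12), the outcome is a simple difference between visits, and the visit-to-visit correlation ρ is 0.3, 0.5 or 0.7. A difference score has SD √(2(1 − ρ)) times the single-visit SD, so d = fraction of gap closed × 1.385 / √(2(1 − ρ)).

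| Fraction of gap closed | ρ = 0.3 | ρ = 0.5 | ρ = 0.7 |
|---|---|---|---|
| Half: d | 0.585 | 0.693 | 0.894 |
| Half: power | 28% | 37% | 55% |
| All: d | 1.171 | 1.385 | 1.788 |
| All: power | 78% | 90% | 99% |

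Moving to a change score can lower or raise power, depending on ρ: with full closure, power is below 90% at ρ = 0.3 and above it at ρ = 0.7. The fraction of the gap that exercise closes also matters greatly, and the article gives no information on it.

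**The case against.** The strongest reply is that the article says only that "the effect size was calculated using" reference 53. It does not say that the MCI-versus-control gap was the quantity used. A within-group figure from that study, or a calculation for another test, cannot be excluded; a repeated-measures interaction with an assumed correlation of 0.5 would imply f of about 0.35 for 24 participants. The stated hypothesis is also directional, and one-sided the required difference falls to 1.23. This stands, and it is why the number cannot be called wrong. It does not rescue the claim: the case-control difference is the only result of that study the article reports, and the planned test is the unpaired t test.

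The stimulation mismatch is also partly answered. The Introduction presents iTBS and 5-Hz rTMS as related measures of LTP-like plasticity and says that iTBS gave similar results in MCI. That makes the choice of assay less troubling, but does not address the exercise contrast.

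Three stronger readings are tempting and unsupported:

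- A reader might infer that the plan assumes cycling fully normalises plasticity. The article does not say so; that would follow only if the whole gap had been used as the effect.
- A reader might infer that a null result will be presented as a well-powered negative. The article does not say how a null would be read. It calls the study a pilot that would inform a larger one.
- A reader might count the lack of a dropout allowance as an error. A condensed article can leave that to the full protocol.

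The pilot label lessens the consequence but does not remove the point, since the article still states a 90% power calculation and a significance test.

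**Conclusion.** The concern holds in a limited form and should be fixed. The 90% power is unsupported for the trial's own comparison, because the source of the effect size, as described in the article, concerns disease versus health and not an exercise effect on change. No arithmetic error is shown in the figure of 24.

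Its size is best expressed as what 12 per arm can detect: a standardised difference of 1.39 in the analysed change for 90% power two-sided, or 1.23 one-sided. These values rest on the noncentral t for the stated test with all 24 analysed. The gap-closing scenarios, 28% to 55% for half and 78% to 99% for all, are illustrations under assumed inputs and should not be quoted as the trial's power. Reference 53 is judged only by the article's description of it.

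**What to change.** Withdraw the claim of 90% power based on reference 53 and replace it with a statement along these lines: 24 is a pilot size; with a two-sided unpaired t test, 12 per arm gives 90% (80%) power only for a standardised difference of 1.39 (1.20) in the T0 to T1 change, or 1.53 (1.32) if 10 per arm are analysed; the 95% confidence interval for the between-group difference will have a half-width of about 0.85 SD.

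Report the between-group difference with its confidence interval, and state that non-significance will not be read as absence of effect.

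The cost is a reworded Power section and a less favourable stated figure. No extra participants are needed.

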### Experimental Design

Individuals will be recruited for assignment to 1 of the 2 equally sized groups: exercise or no exercise. The exercise group will perform the exercise intervention. The no exercise group will serve as the control.

### Experimental Protocol

The dependent measures of synaptic plasticity, cognition, and venous blood BDNF and OCN, will be measured before and after the 4-week intervention (Figure 1).

**Figure 1 figure1:**
[figure not shown]
Dependent measures will be obtained in all participants 2-3 days before (T0) and following the exercise intervention (T1). Synaptic plasticity assessed using transcranial magnetic stimulation, cognitive function assessed by neuropsychological battery, and blood draws for serum BDNF and osteocalcin will be performed before and immediately following the intervention. BDNF: brain-derived neurotrophic factor; OCN: osteocalcin; rTMS: repetitive transcranial magnetic stimulation.

### Exercise Intervention

The exercise group will participate in 3 sessions per week of interval training performed at a self-determined intensity, using a cycle ergometer, for 4 weeks (12 sessions), in line with our previous experience in participant retention [41]. Ratings of perceived exertion (RPE) will be measured using Borg’s 6-20 scale [78]. Participants will be asked to exercise on a stationary bike at an intensity whereby their RPE is deemed “challenging” to them. The perceived effort and RPE rating will likely be different for participants depending on their initial fitness and exercise tolerance. The important aspect is for an individual to feel that the exercise is challenging. The cycling protocol includes 5 one-minute bouts of maximum effort, interspersed with 1.5 minutes of recovery, which will involve cycling at a light intensity (Figure 2). Participants will also perform a 3-minute warm-up and a 2-minute cool-down for a total exercise duration of 17.5 minutes, as we have described [41,74,79]. RPE will be measured by asking the participant to provide their rating at the end of the last interval.

**Figure 2 figure2:**
[figure not shown]
Self-determined intensity interval training protocol on cycle ergometer to be delivered to exercise group.

### Dependent Measures

#### Synaptic Plasticity

Surface electrodes (9 mm AgCl) will be used to record activity from the first dorsal interosseous (FDI) muscle of the right hand. The active electrode will be placed over the muscle belly. To reduce signal noise, dry ground will be placed on the styloid process at the right wrist. Electromyography (EMG) signals will be magnified ×1000 and bandpass filtered between 20 and 2.5 kHz (Intronix Technologies Corporation Model 2024F). An analog-digital converter will be used to digitize data at 5 kHz (Power1401; Cambridge Electronics Design), prior to being analyzed using commercial software (Signal version 7.01; Cambridge Electronics Design). Repetitive TMS will be performed using a 70-mm inner diameter figure-of-8 coil with a Magstim Super Rapid^2^ Plus Stimulator (Magstim). Biphasic magnetic pulses will be delivered over the primary motor area of the dominant hemisphere to find the optimal position for eliciting a MEP in the contralateral FDI muscle [80,81]. The hot spot of the right FDI muscle is defined as the location on the left motor cortex that, when stimulated with rTMS, consistently leads to the largest MEP in the muscle (Figure 3A). This point will be found and registered using Brainsight Neuronavigation and rTMS (Rogue Research).

